### Inclusion criteria

2.4

The inclusion criteria will be as follows.(1)Individuals will be > 18 years of age and < 60 years of age.(2)Participants will meet the diagnostic criteria of DED.^[22]^ The criteria of moderate-to-severe DED are based on the following ophthalmological tests: a Schirmer-I test (SIT) (with the application of cocaine, a local anesthetic) value <10 mm/5 minutes, a tear film break-up time (TBUT) <10 seconds, and corneal fluorescein staining (CFS) ≥ 1.^[2]^ These ophthalmological tests will be performed by the ophthalmologists who do not know the results of the random allocation.(3)Only the single eye with more severe scores or symptoms will be selected to observe the outcome.(4)Participants who can complete the study, treatment, and assessments will be selected.

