#### Primary outcome measure

2.8.1

The primary efficacy endpoint will be the increase from baseline in the SIT value with anesthesia at week 8. The SIT is a diagnostic method used to measure tear secretion,^[24]^ which is measured using tear secretion test paper (Color Bar Schirmer tear test, Eagle Vision, Inc., TN). First, the ophthalmologist responsible for the SIT will use local anesthesia (Alcaine Alcon, Inc., Texas) to arrest reflex tearing. Then, the participants will be requested to look above the eyes, and the ophthalmologists will place the tear secretion test paper under the lower eyelid. Last, the participants will keep their eyes closed for 5 minutes, after which the length of the wet test paper will be measured. The value of SIT equals the length of the wet portion.

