### Sample size and statistical analysis

2.10

The sample size calculation is based on the mean SIT value. According to our pilot trial,^[30]^ the decrease in the mean SIT value in the acupuncture group at week 8 is 3.41 ± 3.04. Based on a previous report, the mean value of the decreases in the artificial tear group is 1.8 ± 1.6.^[2]^ We have used PASS Version 11.0 (International Business Machines Corporation, China) software to calculate a sample size of 120 for each group to provide 90% power to detect a difference of 1.61 between the groups with a 2-sided 5% level of significance, allowing for a 20% dropout rate, and with the participants receiving the treatments and completing the follow-up (60 participants in each group).

SPSS Version 22.0 (International Business Machines Corporation, China) software will be used to perform the statistical analysis. Two-sided tests will be used for all statistical analyses. The level of significance is established at 0.05. Efficiency and safety analyses will be based on all participants at randomization according to the intention-to-treat (ITT) principle. All participants who have accepted randomization will be included in the statistical analysis of data. All original data collected from participants in the trial will be included in the statistical analysis. The data cannot be changed or eliminated at random. The missing data in the case report forms will be replaced randomly by the multiple imputation values.^[31]^

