We will use the mean and standard deviation (SD) to describe continuous data if the data have a normal distribution and the mean and 95% confidence interval (CI) to describe continuous data if the data are skewed. We will use the percentage or 95% CI to describe categorical data. For comparisons with baseline data, we will use a paired *t*-test for continuous data and a nonparametric test for categorical data. For comparisons of the differences between the 2groups, T-tests or Mann–Whitney *U* tests will be used for comparisons between continuous variables, and chi-square tests or Fisher's exact tests will be used for comparisons between categorical variables, as appropriate. For assessing safety in the trial, the investigator will present the AEs and adverse reactions with tables, which will comprise the categories of AEs, the severity of AEs, the incidence of AEs, and correlation with the treatment. Every participant with serious AEs will stop receiving the intervention. All details will be reported in a timely manner.

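### The unadjusted two-group test of change in SIT uses baseline only by subtraction; adjusting for baseline as a covariate would be more precise at no cost

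*Protocol article*

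**What the plan says.** The primary endpoint (Protocol article, section 2.8.1) is a change score: "The primary efficacy endpoint will be the increase from baseline in the SIT value with anesthesia at week 8". Section 2.10 sizes the trial on mean changes: "the decrease in the mean SIT value in the acupuncture group at week 8 is 3.41 ± 3.04" and "the mean value of the decreases in the artificial tear group is 1.8 ± 1.6", aiming "to provide 90% power to detect a difference of 1.61 between the groups" "with a 2-sided 5% level of significance".

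The between-group method in section 2.10 is "For comparisons of the differences between the 2groups, T-tests" or Mann–Whitney U tests for continuous variables. No covariate, analysis of covariance or mixed model is named anywhere in the article. Paired t-tests are listed for within-group comparisons with baseline.

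Section 2.8.2 schedules a baseline measurement of SIT, the symptom VAS, OSDI and TBUT. It does not say whether VAS, OSDI and TBUT are compared between groups as changes or as visit values.

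Two entry rules in section 2.4 bear on the point. SIT must be below 10 mm in 5 minutes, and "Only the single eye with more severe scores or symptoms will be selected to observe the outcome".

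**The concern.** A t-test on change scores assumes in effect that week-8 SIT moves one for one with baseline SIT. Both entry rules select low readings, and low readings selected in this way tend to rise on retest whatever the treatment. Follow-up then moves less than one for one with baseline, and change is negatively related to baseline. Two consequences follow, which are two views of one inefficiency:

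- The variance of the treatment difference contains a component that baseline could explain, so the confidence interval is wider than it need be.
- In the one sample that the trial will have, the arm that happens to start lower tends to show the larger gain, and the unadjusted estimate carries that shift.

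At stake is precision, and how far a reader can trust the estimate if the baseline table shows a visible difference in SIT. The article names the test, so this is a stated choice and not something left open for a statistical analysis plan.

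**Working it through.** **Inputs from section 2.10.** Difference 1.61 mm (3.41 − 1.8); SDs of change 3.04 and 1.6; two-sided 5%; 90% power; 20% dropout.

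**The plan's own figure.** The mean of the two variances is (3.04² + 1.6²)/2 = (9.2416 + 2.56)/2 = 5.9008, so the pooled SD is 2.429. With the normal approximation, n = 2 × (1.96 + 1.2816)² × 5.9008 / 1.61² = 47.8, that is 48 evaluable per group, and 48/0.8 = 60 per group. This matches the 60-per-group wording. The same sentence also says 120 for each group, which these inputs do not reproduce. The 60-per-group reading is used below.

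**Planned test.** SE = √((9.2416 + 2.56)/48) = 0.496 mm. Power at 1.61 mm is 90.1% by the normal approximation and 89.3% by the Welch t-test, which allows for the unequal SDs.

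**Effect of adjustment.** Let b be the slope of week-8 SIT on baseline and SDb the baseline SD, both taken as common to the two arms. Then

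Var(change) = residual variance + (1 − b)² × SDb².

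The covariate model removes the second term. The documents give neither b nor SDb. Assumed ranges: SDb 2 to 2.5 mm (entry cuts the range at 10 mm) and b 0.5 to 0.8. Power is for the Welch test at 48 completers per group.

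| SDb (mm) | b | (1 − b)² × SDb² | Cut in variance (÷ 5.9008) | Power |
|---|---|---|---|---|
| 2.0 | 0.8 | 0.16 | 2.7% | 90.1% |
| 2.5 | 0.8 | 0.25 | 4.2% | 90.5% |
| 2.0 | 0.5 | 1.00 | 16.9% | 93.9% |
| 2.5 | 0.5 | 1.5625 | 26.5% | 96.1% |

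In completers, 48/(1 − 0.027) = 49.3 and 48/(1 − 0.265) = 65.3, a gain equal to about 1 to 17 per group.

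**Second parameterization.** Assume equal variances at baseline and week 8 with correlation ρ. The variance of the adjusted estimate relative to the change-score estimate is (1 − ρ²)/(2(1 − ρ)) = (1 + ρ)/2. That is 0.65 at ρ = 0.3, 0.75 at 0.5 and 0.90 at 0.8. The direction is the same; the size again depends on an assumption.

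**Movement with chance imbalance.** The change-score estimate shifts by (1 − b) times the baseline difference between arms, in the opposite direction. With 60 randomized per arm, the SE of that baseline difference is SDb × √(2/60).

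- At a one-SE imbalance the shift is 0.2 × 2 × 0.1826 = 0.07 mm to 0.5 × 2.5 × 0.1826 = 0.23 mm.
- At a 1.96-SE imbalance, equalled or exceeded in about 5% of trials, it is 0.14 to 0.45 mm, or 9% to 28% of 1.61 mm.

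**The other sample-size wording.** With 120 per group and 96 completers, unadjusted Welch power is already 99.5%, and the 1.96-SE shift is 0.10 to 0.32 mm. The relative cut in variance is unchanged, but there is almost no power left to gain.

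**The case against.** The strongest reply is that the plan is coherent and valid. Endpoint, sample-size inputs and the t-test all fit change from baseline, and the 60-per-group figure reproduces. Regression to the mean acts on both arms alike in expectation. The variation due to chance imbalance is already inside the change-score SE, so the 5% error rate holds. All of this stands. Imbalance and lost precision must not be counted as two separate costs.

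It is also fair that the size rests on an assumed SD and slope, and that at the low end the gain is about one completer per group. The near-twofold ratio of SDs comes from two different sources, a pilot and a previous report, and may not recur in this trial. A robust standard error is harmless if it does not.

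A reader might infer three stronger things that the documents do not support:

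- That baseline is ignored for the primary outcome. It is not: the endpoint is the increase from baseline, so baseline is subtracted.
- That baseline is ignored for every continuous secondary outcome. The article does not say whether VAS, OSDI and TBUT are compared as changes or as visit values. Either form leaves chance imbalance in the estimate, in opposite directions, so the remedy is the same. Treatment acceptance is measured only at week 8 and has no baseline to adjust for.
- That the primary result is biased or the trial underpowered for this reason. Neither follows.

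What the reply does not meet is that a better method is available from data already scheduled, and that the article names the weaker one.

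**Conclusion.** The point holds as a free improvement: a loss of efficiency, with an estimate that depends on the baseline imbalance that happens to occur, and not an error of validity. For the primary outcome, baseline is used with its slope fixed at 1, where the entry rules make a smaller slope likely. On the 60-per-group reading, with an assumed baseline SD of 2 to 2.5 mm and slope of 0.5 to 0.8, adjustment cuts the variance of the treatment difference by about 3% to 26% and takes power from about 89% to between 90% and 96%. The lower end is negligible and the upper end is useful; the documents do not show where this trial lies. For the secondary outcomes no size can be given, because neither the form of the comparison nor any SD is stated.

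**What to change.** In section 2.10, name one primary analysis: a linear model of week-8 SIT (or, equivalently, its change from baseline) on treatment, with baseline SIT as covariate and a heteroscedasticity-robust standard error. Report the adjusted mean difference with its 95% CI. Use the same model for SIT at weeks 4 and 32 and for VAS, OSDI and TBUT, each with its own baseline. Keep the unadjusted t-test as a sensitivity analysis.

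The sample size need not change, since the existing calculation is for the unadjusted test and is conservative for the adjusted one. The cost is one or two sentences of wording, with no extra data, visits or participants. The change should be made before outcome data are examined by group.

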### Quality control

2.11

The acupuncture practitioners responsible for the acupuncture treatments must have a minimum of 5 years of clinical experience. All of the investigators will take a one-day training course for this trial. This training course will cover the study protocol, acupuncture operation, precautions for drug use, the recording method for CRF, disposal of bleeding, a researcher duties and research monitoring. Full-time researchers who are not aware of the random allocation of groups will be responsible for the assessments of all scales. During the trial, supervisors will check on case reports and acupuncture treatments once a month. Drop-outs, withdrawals (with the reasons), and the compliance of all participants will be recorded in detail throughout the treatment and follow-up period. Two postgraduates (not involved in the trial) will input the data independently and verify the database together.

### Ethics and dissemination

2.12

The study protocol is in accordance with the principles of the Declaration of Helsinki,^[32]^ was approved by the Ethics Committee of Guang’anmen Hospital of China Academy of Chinese Medical Sciences (approval number 2018-012-KY-01) on April 19, 2018 and was registered on April 23, 2018, at http://www.chictr.org.cn/ (ref. ChiCTR1800015831). All important protocol modifications will be submitted to the Ethics Committee of Guang’anmen Hospital. The researchers will inform all participants of the potential risks and benefits of the study. Informed consent will be obtained for all participants from either the participant or the participant's legal representative. All participants will be required to be able to understand written instructions, complete the examination and assessment forms. The personal information of all participants will be hidden from other users and stored in a specific cabinet with a lock. Statistics and monitoring managers will have the right to obtain the final study data set. To prevent the participants from suffering harm from trial participation, we will provide corresponding treatment and medical consultations with the ophthalmologist for free. We will disseminate the results of this study in meetings or publications when the trial is completed.

## Discussion

3

The aim of this study is to evaluate the efficacy and safety of using acupuncture at a single BL1 acupuncture point for improving tear secretion and other symptoms of patients with moderate to severe DED. Two systematic reviews and several previous studies have shown that acupuncture is effective in the treatment of DED. For example, Jeon et al conducted an observational study on the acupuncture treatment of DED in the Korean Oriental medicine hospital.^[16]^ The results of the trial showed that acupuncture treatment could effectively improve the symptoms of DED and tear secretion. In a clinical study comparing the effects of acupuncture and artificial tears on DED, which was conducted by Kim et al^[15]^ in South Korea, a better curative effect was observed during the 8-week follow-up period in the acupuncture group. Thus, to reveal whether acupuncture treatment has a longer lasting effect than artificial tear treatment, our trial will carry out a 24-week follow-up. Although several studies have shown that acupuncture may be effective for DED, a negative result of a clinical study has been reported. A randomized, double-blind trial with acupuncture versus sham acupuncture for DED was conducted by Shin et al^[33]^ in the Korea Oriental medical hospital. After 4 weeks of treatment, the trial results showed that acupuncture did not offer any significant improvement over sham acupuncture. The result of the trial suggests that the effect of acupuncture in the treatment of DED is controversial. Different results may occur due to different acupuncture points, acupuncture manipulation, primary outcomes, treatment duration, outcome measures, severity of disease, sample sizes, or other factors.

The main difference from previous studies is that only a single acupuncture point will be used. In this study, we will not use the conventional acupuncture manipulation, but instead of puncturing the BL1 acupuncture point from the inside of the eyelid to a depth of 0.5 inches. A large amount of tear fluid flows out of the eyes of the participants after each acupuncture treatment, which can guarantee a curative effect. The second difference from previous studies is that the primary outcome of our study is the measurement of tear secretion with the SIT. The most obvious advantage of our acupuncture at a single acupuncture point by special acupuncture manipulation in this study is to promote the tear secretion. Third, this study will involve a treatment duration of 8 weeks, which is an appropriate treatment duration for acupuncture therapy for moderate to severe DED. Moreover, according to the suggestion of the DEWS, any clinical study that involves the treatment of DED with artificial tears should be performed for at least 6 to 8 weeks. Fourth, acupuncture manipulation of that point will only last for 1 minute in our trial, which is different from other acupuncture operation for 20 to 30 minutes. The use of this acupuncture method in the treatment of DED may be more effective and convenient based on our previous clinical experience.

The characteristics of DED include reduced tear secretion and ocular surface damage. It is generally believed that the obstruction of tear secretion is an important pathogenesis of DED.^[34]^ The mechanism of acupuncture at the BL1 point for the treatment of DED is derived from the anatomy and physiology of acupuncture points. According to the anatomical structure, there are lacrimal sacs and lacrimal canaliculi below BL1, which can stimulate tear secretion via acupuncture and manipulation. To achieve a certain depth of acupuncture, the needles will be inserted into BL1 from the inside of the eyelid. Moreover, repeated acupuncture manipulation can improve the function of the lacrimal sac to secrete tears, which explains the persistent long-term effect after acupuncture treatment.

There are several limitations in our trial. First, the trial is conducted in a single center. Thus, regional differences cannot be shown. Second, because the trial will be conducted in the hospital of traditional Chinese medicine, many participants may have a higher expectation of acupuncture therapy. Third, participant blinding is impossible due to wide differences between acupuncture and artificial tear treatments. Fourth, we are not conducting a placebo control trial because we consider that the use of sham acupuncture may not provide sufficient sensitivity and may not meet ethical guidelines.
